### Measurements

All participants in both the intervention and the comparison schools will be assessed prior to the beginning of the programme (baseline assessment), after the final session of the intervention (post-intervention assessment) and 3 months afterwards (follow-up assessment).

#### Socio-demographic characteristics

Adolescents will answer questionnaires regarding their socio-demographic backgrounds, including gender, ethnicity, age, date of birth, number of family members living together, number of siblings, academic achievements and parents’ background (educational level, occupation and monthly income).

#### Anthropometric measurements

Anthropometric measurements will be carried out by trained personnel. Body weight will be measured using Tanita Glass Digital Bathroom Scale Model HD-382 (Tanita Corporation, Japan), while height will be measured by using SECA 206 height mechanical measuring tape (SECA, Germany). Body weight and height will be used for BMI calculation using the following formula:$$ \mathrm{B}\mathrm{M}\mathrm{I} = \mathrm{weight}\ \left(\mathrm{kg}\right)/\ {\mathrm{height}}^2\left({\mathrm{m}}^2\right). $$

BMI-for-age (z-score) (BAZ) will be determined using BMI and height values. BAZ values will be used to categorize the status of each participant’s body weight in line with WHO Growth Reference for individuals 5–19 years old [30]. BAZ cut-off points are as followed: Severe thinness: <−3 SD; thinness: <−2 SD; normal weight: ≤ − 2 SD and ≥ 1 SD; overweight: > +1 SD; and obesity: > +2 SD.

Waist circumference will be measured by using a measuring tape. Abdominal obesity status will be determined by referring to the cut-off point of the 90th percentile of waist circumference of adolescents aged 12–16 years [31]. Omron HBF-306 Body Fat Analyzer Scale (Omron Corporation, Japan) will be used to measure the percentage of body fat. The instruments used were adequately calibrated; and adolescents were asked to remove their shoes and empty their pockets before measurement.

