## Background

Globalisation, urbanisation and economic development in the past century have had a negative impact on eating habits and exercise in both developed and developing nations. This impact is evident in modern adolescents’ eating and physical activity regimens. In Malaysia, adolescents, individuals aged 10–19 years, make up a population of 5.5 million i.e., 18.9 % of the entire Malaysian population [1].

At the age of adolescence, major physical, psychological and social changes occur. For instance, this stage of development is the second chance of catch-up growth before entering adulthood. Inadequate intake of carbohydrates, proteins, fat, vitamins and/or minerals has been shown to have severe consequences on growth during this stage, and is associated with delayed onset of puberty [2]. This is because nutritive demands of adolescence are only second to infancy. Excessive food intake, however, has also been shown to have detrimental effects on adolescents’ health, such as increasing their susceptibility to diseases and precipitating diabetes, heart disease and hypertension [3].

Overweight and obesity are major public health issues in both developed and developing countries. Between 1980 and 2013, the prevalence of overweight and obesity in developed countries remarkably increased from 16.9 and 16.2 % to 23.8 and 22.6 % in male and female adolescents respectively; whereas in developing countries, a whopping 9.8 % increase in the number of overweight and obese adolescents was observed around the same period of time [4].

In Malaysia, high percentages of overweight and obese adolescents, as well as adolescents suffering from disordered eating have been reported. According to the National Health and Morbidity Survey (NHMS), the prevalence of obesity in Malaysian adolescents increased dramatically between 2011 and 2015 from as low as 6.1 % [5] to 11.9 % [6]. Alarmingly, estimates from a separate nationwide study showed that as of 2015, 14.2 % of Malaysian adolescents aged 12–19 were overweight, while 10.1 % were rather obese [7].

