Healthy Lifestyle in Children (HELIC) [23], Healthy Kids Programme [24], Body Image Education Package [25] and the Malaysian Childhood Obesity Treatment Trial (MASCOT) [26] are a few of many school-based interventions that had been implemented in Malaysia. However, most of these interventions have rather been stand-alone programmes in the sense that they focused either on the prevention of obesity or the prevention of disordered eating. As far as our knowledge goes, Malaysia has not seen a comprehensive intervention programme that promotes all three components of a healthy life: healthy eating, active lifestyle and positive body image.

‘Eat Right, Be Positive About Your Body and Live Actively’ (EPaL) is an integrated health education intervention, which developed to prevent overweight and disordered eating among Malaysian adolescents. This intervention was formulated with the understanding that obesity, disordered eating, and extreme weight loss practices were strongly correlated and shared the same risk factors. Hence, it delivered a coherent message while tackling a broad spectrum of eating- and weight-related health issues. Unlike Healthy Buddies, EPaL did not use a one-to-one approach [22], but rather involved training a group of adolescents to become peer educators who then led others to fully implement the intervention. It differed from MABIC as it stipulated that the trainees be adolescents rather than educators or health care providers, such as tutors, clinical psychologists and nurses [20].

This paper describes the protocol for an integrated health education intervention namely ‘Eat Right, Be Positive About Your Body and Live Actively’ (EPaL), a primary prevention which aimed to promote healthy lifestyle, which including healthy eating, positive body image and active lifestyle, in preventing overweight and disordered eating among first and second year secondary school adolescents. In the present work, adolescents were used to ascertain whether or not EPaL could serve as an effective tool to promote health in Malaysian adolescents and reduce the incidence of overweight and disordered eating. The intervention was developed by taking consideration on risk factors and cultural background of Malaysian population, which might be different from other countries. The risk factors of interest were determined beforehand by carrying out a wide survey amongst secondary school adolescents throughout Malaysia.

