### Setting, recruitment and participants

Two schools were randomly selected in the district of Hulu Langat, the state of Selangor, Malaysia. One school will randomly chose to receive the intervention, while adolescents in the other served as the comparison group. Selection of the schools will be performed by means of a draw from a list of schools in Selangor, obtained from the website of the state’s Department of Education. Only schools that met the inclusion criteria (coeducational, multiracial, non-residential and non-religious) were included in the draw. Adolescents who were Form 1 or 2 students and 13–14 years old; and whose parents consented to the intervention met the criteria for inclusion in the study.

A seminar will be held for the parents and teachers of Form 1 and 2 students in which EPaL will be introduced. Parents and teachers were asked to promote the programme to the students. Recruited students were presented with the research’s information sheet and consent letters to be read and filled by them and their parents. Written consent letters were collected from participating adolescents and their parents prior to the intervention. Thereafter, the students were subjected to the EPaL intervention programme over the course of 16 weeks in their school. They were assessed in three points of assessments, which are prior to the intervention (baseline), after the final session of the programme (post-intervention) and 3 months thereafter (follow-up).

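### A follow-up of about 29 weeks, with BMI-for-age z-scores stated only as a means to assign weight categories, is a weak basis for a claim to prevent overweight or reduce its incidence

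*Protocol article*

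**What the plan says.** In the protocol article, the Background says the study is to ascertain whether EPaL can "promote health in Malaysian adolescents and reduce the incidence of overweight and disordered eating". The Abstract and the description of the intervention also give prevention of overweight as the purpose.

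Setting, recruitment and participants has students take part "over the course of 16 weeks in their school", with assessments at baseline, "after the final session of the programme (post-intervention) and 3 months thereafter (follow-up").

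Anthropometric measurements states one use for the z-score: "BAZ values will be used to categorize the status of each" student's weight, with WHO cut-offs at -3, -2, +1 and +2 SD. Waist circumference and percentage body fat are also measured.

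Data analysis assigns t-tests to continuous variables between groups, chi-square to categorical variables, and repeated-measures ANOVA to changes within groups. It does not say which of these applies to weight.

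The sample size of 234 per group comes from the proportions with disordered eating among overweight/obese adolescents (40.3%) and other adolescents (27.9%). No calculation addresses weight status.

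The only Malaysian time trend in the article is for obesity, which "increased dramatically between 2011 and 2015 from as low as 6.1 % [5] to 11.9 % [6"].

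**The concern.** Prevention of overweight is a statement about how many students cross a threshold. Over roughly seven months few are likely to cross it, so a comparison of weight categories carries little information about whether EPaL works. Categorising BAZ also drops movement within a category, which is most of what a study of this length can measure.

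Two misreadings are at stake. A null result on weight status could be reported as showing that EPaL does not prevent overweight, and a chance difference could be reported as prevention. The Discussion offers EPaL as a model for later programmes in Malaysia, so the wording of the conclusion matters.

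**Working it through.** **1. The plan's own figure.** For 40.3% versus 27.9%, 80% power and two-sided 5%, the pooled normal formula gives 229 per group and the arcsine formula gives 228 (h = 0.263). The stated 234 is within 3% of these. It is sized for a difference in disordered eating and gives no assurance about weight.

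**2. Length of observation.** 16 weeks + 3 months (about 13 weeks) = 29 weeks, or 29/52 = 0.558 year.

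**3. New cases on the article's trend.** (11.9 - 6.1)/4 = 1.45 points a year. Then 1.45 x 0.558 = 0.81 points, and 0.0081 x 234 = 1.9 students per group. This is a rough proxy: it is a net change in obesity prevalence between surveys, not the rate at which individual students become overweight. Higher incidences are therefore assumed as well.

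**4. Power for new cases.** Exact power of Fisher's test, two-sided 5%, 234 independent students per group, risk = annual rate x 29/52:

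| Annual incidence | Risk over 29 weeks | Expected cases, comparison group | Power, all prevented | Power, half prevented |
|---|---|---|---|---|
| 1.45% (trend as proxy) | 0.81% | 1.9 | 1.3% | 0.5% |
| 3% (assumed) | 1.67% | 3.9 | 20% | 4.3% |
| 5% (assumed) | 2.79% | 6.5 | 64% | 10% |
| 8% (assumed) | 4.46% | 10.4 | 95% | 19% |
| 10% (assumed) | 5.58% | 13.1 | 99% | 25% |

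With no cases in one group, the other needs at least 6 for significance: 5 versus 0 gives p = 0.061 and 6 versus 0 gives p = 0.030. The table counts all 234 as at risk. Leaving out students who are already overweight would reduce the denominator and, at the same risk, the power.

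**5. Prevalence comparison.** This allows downward moves too. The Background gives 14.2% overweight and 10.1% obese. Taken as separate categories they sum to 24.3%, or 0.243 x 234 = about 57 students per group. Power for 24.3% versus 14.3% (pooled normal formula) is 78%. For a difference of 0.81 points it is about 4%.

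**6. Continuous BAZ.** Detectable difference in change at 80% power = (1.96 + 0.84) x SD x sqrt(2/234). The article gives no SD of change. Assuming 0.3 to 0.5, the result is 2.80 x 0.3 x 0.0924 = 0.08 to 2.80 x 0.5 x 0.0924 = 0.13 z-units, again for independent students.

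**The case against.** A reader might infer that the protocol commits to analysing BAZ only as categories. The text does not support that. It states one use and excludes no other, it plans t-tests for continuous variables, and the Abstract lists body weight among the parameters. The choice of analysis form is also something an article may leave to the full plan. What stands is narrower: the stated use is categorisation, and it sits beside an aim worded as prevention and reduced incidence.

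A reader might also infer that no prevention effect could be seen, or that the comparison is bound to be null. That does not hold either. The obesity trend is a poor proxy for overweight incidence at 13 to 14 years, an age at which the Background says body fat rises. The article's two obesity figures for 2015 (11.9% and 10.1%) differ by 1.8 points, more than one year of the trend. At higher assumed incidences complete prevention would be detected. Counting only new cases also ignores the roughly 24% who could move down a category.

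These points remove the absolute wording. They do not rescue the category comparison for a realistic effect: halving new cases reaches only 25% power at 10% a year, and prevalence would have to fall by about 10 points.

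Finally, parts of the article are milder. The Abstract speaks of contributing to prevention, and the Discussion of a positive change in body weight status. The Background's incidence wording is still there, and it should be brought into line with what 29 weeks can show.

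**Conclusion.** The point holds in this limited form. An analysis of weight categories over about 29 weeks has low power for a realistic effect: 0.5% for halving new cases on the trend proxy, and about 4% to 25% at assumed incidences of 3% to 10% a year. Complete prevention is detectable only towards the upper end of that range. The protocol does not forbid a better analysis, but it neither names one nor limits its conclusion to match.

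The figures rest on 234 students per group treated as independent, on assumed incidences above the trend, and on an assumed SD of BAZ change. With one school per group the real information is less than these figures suggest. This is a worthwhile, inexpensive improvement to the weight outcome and to the wording of the claim. It does not show that the trial as a whole is uninformative.

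**What to change.** Name as the weight outcome the between-school difference in change in continuous BAZ from baseline to the 3-month follow-up, adjusted for baseline BAZ. Report overweight/obesity, and thinness separately, as descriptive categories. Word the weight conclusion as a short-term effect on BMI-for-age, and withdraw any statement that the trial shows prevention or reduced incidence of overweight.

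This needs no new visits, measurements or participants, because BAZ is already to be derived for each student. The cost is a more modest headline claim on overweight. The change does not separate the effect of EPaL from differences between the two schools, and that limitation should be stated beside the result.

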#### Stages of change

According to the Transtheoretical Model, five stages of change will be identified: Pre-contemplation, contemplation, preparation, action and maintenance for healthy diet [32], breakfast, food portion size, screen-viewing time (television/ video/ DVD) [33] and physical activity [34]. This model will be used to determine adolescents’ adherence to a healthy lifestyle before and after the implementation of the intervention. This will provided a clear view of the progress that the participants made in terms of adopting and maintaining health behaviours [35].

#### Disordered eating

The Eating Attitudes Test-26 (EAT-26) is a widely used instrument to assess eating disorders based on attitudes, feelings and behaviours [36] and will, hence, used in the present study. The EAT-26 consisted of 26 items with six response categories each, ranging from 1 (never) to 6 (always). A score higher than 20 indicated disordered eating. Items on EAT-26 scale allowed three subscales to be calculated, known as dieting; bulimia and food preoccupation and oral control.

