**Methods/Design:**

Following quasi-experimental design, the intervention is conducted in two secondary schools located in the district of Hulu Langat, Selangor, Malaysia. Adolescents aged 13–14 years will be included in the study. A peer-education strategy is adopted to convey knowledge and teach skills relevant to achieving a healthy lifestyle. The intervention mainly promoted: healthy eating, positive body image and active lifestyle. The following parameters will be assessed: body weight, disordered eating status, stages of change (for healthy diet, breakfast, food portion size, screen viewing and physical activity), body image, health-related quality of life, self-esteem, eating and physical activity behaviours; and knowledge, attitude and practice towards a healthy lifestyle. Assessment will be conducted at three time points: baseline, post-intervention and 3-month follow-up.

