### Sample size calculation

The sample size calculation was based on the differences between groups (overweight and obese; and non-overweight and non-obese) in the proportion of having disordered eating. The value was taken from the outcome of needs assessment study, which was conducted involving 9677 adolescents aged 12–19 years throughout Malaysia. Based on the study, the proportion of overweight and obese adolescents who were having disordered eating was 40.3 %, whereas the proportion of non-overweight and non-obese adolescents who were having disordered eating was 27.9 %. Assuming a power of 80 % and a level of significance of 5 %, we needed 234 participants for each intervention and comparison groups, respectively. The effect size for proportions was estimated by the differences in the arcsine transformations of the respective proportions. The medium effect size of 25.4 % was obtained.

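### The EAT-26 item coding (1 to 6 on 26 items) and the cut-off (above 20) cannot both apply: summed codes start at 26, so every complete respondent would be classed as having disordered eating

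*Protocol article*

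**What the plan says.** In the Protocol article, Measurements, the Disordered eating section describes the instrument as "26 items with six response categories each, ranging from 1 (never) to 6 (always). A score higher than 20 indicated disordered eating". The only other scoring statement there is "Items on EAT-26 scale allowed three subscales to be calculated, known as dieting; bulimia and food preoccupation and oral control". It gives no conversion of responses to item scores, no rule for forming the total, and no score range.

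Disordered eating status is a named outcome. The abstract says "The following parameters will be assessed: body weight, disordered eating status, stages of change", and the assessments are at baseline, after the intervention and 3 months later. Preventing disordered eating is one of the two stated aims, alongside preventing overweight.

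The Sample size calculation section uses two proportions from the needs-assessment survey: "the proportion of overweight and obese adolescents who were having disordered eating was 40.3" per cent, and "the proportion of non-overweight and non-obese adolescents who were having disordered eating was 27.9" per cent. It does not name the questionnaire or the scoring behind them. The Data analysis section assigns chi-square to categorical variables and t-tests to continuous ones.

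**The concern.** A classification rule is useful only if its cut-off falls inside the range of the score. Here the item coding and the cut-off stand in adjacent sentences, and the cut-off falls outside the range that the coding produces. Anyone who derives disordered eating status from this text would obtain a constant.

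What is at stake is a binary outcome tied to one of the trial's two aims, and the same kind of outcome (a proportion with disordered eating) on which the only sample size calculation rests. A constant carries no information about the intervention.

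**Working it through.** **Inputs** (Disordered eating section): 26 items; lowest response code 1; highest response code 6; a case is a score above 20.

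**The plan's own figure.** The section on scoring states no range to reproduce. The one related figure is 234 per group in the Sample size calculation section. The test is taken as two-sided, since the article does not say.
- Arcsine effect size: h = 2·arcsin(√0.403) − 2·arcsin(√0.279) = 0.2626.
- n = 2·((1.960 + 0.842)/0.2626)² = 227.7, so 228 per group.
- The pooled two-proportion formula gives 229.
- Both are within 3% of 234 (228/234 = 0.974), so the figure is reproduced closely. No EAT-26 item code or cut-off enters this calculation.

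**Reading 1: the score is the sum of the codes.**
- Minimum = 26 × 1 = 26.
- Maximum = 26 × 6 = 156.
- The minimum of 26 is above 20, so a student who answers never to every item is a case. All complete respondents are cases.
- With the planned 234 per school, the table is 234 cases and 0 non-cases in each. The difference in proportions is 100% − 100% = 0. The non-case column is empty, its expected counts are 0, and the chi-square statistic is undefined.
- The same holds at each assessment, so there is no within-school change either.

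This concerns complete forms. If blanks counted as 0, a form with never on every answered item would fall to 20 only with 26 − 20 = 6 items blank. The section does not address missing items.

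**Reading 2: the score is the mean of the codes.**
- Range = 1 to 6. The maximum of 6 is below 20, so nobody is a case. The status is again constant.

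**Is there another rule in the article?** The subscale sentence gives no item counts or weights, and nothing ties the cut-off to a subscale. No other section gives a recoding for the EAT-26. By contrast, the section on health-related quality of life does map the PedsQL raw responses to their scored values.

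**What a working rule would need.** The lowest response must score low enough for totals of 20 or less to occur. Purely as an illustration, and not taken from the documents: items scored 0 to 5 would give totals from 0 to 26 × 5 = 130, and a cut-off of 20 would then lie inside the range.

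**Comparison with the planning proportions.** A rule that flags everyone, or no one, cannot yield 40.3% or 27.9%. If those figures came from the EAT-26, some other scoring was used.

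**The case against.** The strongest reply is that the numbers 1 to 6 label response categories and are not said to be the scored values. The article never says that the total is their plain sum. It is also a condensed account: for the Rosenberg scale, the TFEQ-R18 and the practice items of the KAP-ELQ it gives labelled codes and leaves the scoring unstated. The EAT-26 is cited to its source, and the full protocol may carry the scoring.

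Part of this stands. Plain summing is an inference, so the 100% figure depends on it. But the point is not that scoring detail is absent. For this scale the article prints a coding and a cut-off together, and neither the sum nor the mean of that coding is compatible with that cut-off.

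Three stronger readings are tempting, and the documents support none of them.

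- **The planning figures and the trial outcome are on different scales.** The Sample size calculation section names no instrument or scoring, and the same research programme ran the survey. One discriminating rule used in both studies, and misdescribed here, fits the text equally well.
- **The trial cannot detect any effect on disordered eating.** That would require the team to apply the literal rule and leave uncorrected a baseline at which every student is a case. If item responses are recorded, the status can be rederived. Analyses of subscale or total scores as continuous variables do not use the cut-off.
- **The sample size is wrong because of this.** It is computed from the two proportions alone and is unaffected.

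**Conclusion.** The concern holds as an error in the rule as written. If the codes are summed, 100% of complete respondents are classed as having disordered eating at every assessment; if they are averaged, 0% are. Either way, the status cannot vary between schools or over time.

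The conclusion rests on two things: the printed codes being the scored values, and the article containing no recoding. The second has been checked against the text. The first is the natural reading but is not stated, and it is probably where the error lies, with response codes printed where scored values belong. The planning proportions point the same way, since they imply a rule that separates cases from non-cases, but they are not proof because their instrument is not named.

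The finding does not show that any data were misclassified. It shows that a target outcome cannot be derived from the published description, and this should be corrected before disordered eating status is analysed.

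**What to change.** In the Disordered eating section, reconcile the item coding with the cut-off. State:

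1. how each of the six responses is converted to an item score;
2. how the total is formed and the range it can take;
3. the cut-off on that total.

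All three should follow the source that the article cites for the instrument. One rule should then apply at baseline, post-intervention and follow-up in both schools.

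In the Sample size calculation section, name the instrument and scoring behind 40.3% and 27.9%, and confirm whether they match the trial's rule.

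The cost is a sentence or so in each section and a check that the scoring syntax agrees. No additional data collection or change to the sample size follows from this point.
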